### Secondary study parameters/endpoints

Secondary outcome measures are anatomical changes due to HTO and pain and function scores. Parameters are tibial slope (Moore-Harvey and Dejour-Bonin); patellar height (Insall-Salvati and Caton Index) and difference in leg length (cm) one year after surgery; and pain severity (VAS; range 0–10), knee function and quality of life (KOOS), and walking distance (km) at six weeks, three months, six months and one year after surgery.

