### Study procedures

Preoperatively as well as six weeks, six months and one year postoperatively, patients will visit the outpatient clinic. Routine physical examination will be performed by the orthopedic surgeon.

Primary outcome measure–achievement of an overcorrection of 4° valgus alignment / hip-knee-ankle angle (HKA, in degrees)–will be measured after one year on a whole-leg radiograph (WLR) standing on one leg. The continuous differences in achievement of a valgus overcorrection and the deviation from 4° valgus are determined. A dichotomous outcome is achievement of a 2-6° valgus alignment.

Secondary outcome measures, posterior tibial slope (Moore-Harvey and Dejour-Bonin), patellar height (Insall-Salvati and Caton Index) and difference in leg length (cm) one year after surgery will be obtained. Pain severity (VAS; range 0–10), knee function and quality of life (KOOS), and walking distance (km) six weeks, three months, six months and one year after surgery will also be obtained.

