### Sample size calculation

The sample size was calculated based on an expected increase of the success rate from 60% in the closed wedge HTO to 85% in the combined wedge HTO. A successful operative result is defined as achievement of a 2-6° valgus alignment. To detect such a difference with α= 0.05 and a power of 80%, we need to include 50 patients in each study group. To adjust for possible loss to follow-up, a total of 110 patients will be included in the study.

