### Statistics

All data will be analyzed according to an intention-to-treat principle, implying that all patients who are randomized will be included in the analyses, and that they will be analyzed according to the group to which they were allocated. For those patients who will be lost to follow-up or will be re-operated during follow-up, the last available measurement or the last measurement will be forwarded (Last Value Carried Forward technique).

A multivariable linear regression method will be used to analyze the impact of LCW versus CWO HTO on postoperative alignment, posterior tibial slope, patellar height, leg length, VAS, KOOS, walking distance and patients with adverse events at the one-year follow-up. A multivariable logistic regression method will be used for the dichotomous outcome measures. Gender, age and baseline values for HKA angle, VAS knee, KOOS, walking distance, medial osteoarthritis more than joint space loss alone, and concurrent OA of the lateral compartment will be considered as possible confounders and are included in the regression models only if they change the relationship between dependent variable and type of HTO by at least 10%. The SPSS program will be used for the statistical analyses and a p-value of 0.05 is considered statistically significant.

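### VAS, KOOS and walking distance are secondary endpoints at four follow-up times, but the only stated model compares the arms at one year

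*Protocol article*

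**What the plan says.** **Endpoints.** In the protocol article, Secondary study parameters/endpoints, tibial slope, patellar height and leg length are tied to one year. Pain (VAS, 0 to 10) is given a longer schedule, together with "knee function and quality of life (KOOS), and walking distance (km) at six weeks, three months, six months and one year after surgery". Study procedures repeats the four times: "walking distance (km) six weeks, three months, six months and one year after surgery will also be obtained".

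**Visits.** Study procedures also states: "Preoperatively as well as six weeks, six months and one year postoperatively, patients will visit the outpatient clinic". No clinic visit is listed at three months.

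**Analysis.** Statistics says: "A multivariable linear regression method will be used to analyze the impact of LCW versus CWO HTO on postoperative alignment". The list of outcomes for that model ends with "leg length, VAS, KOOS, walking distance and patients with adverse events at the one-year follow-up". No other model is given for the continuous scales.

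**Incomplete follow-up.** For patients lost to follow-up or re-operated, "the last available measurement or the last measurement will be forwarded (Last Value Carried Forward technique".

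**The concern.** The endpoint section and the analysis section do not cover the same times. The longer schedule for the patient-level scales looks deliberate, because the same section restricts the radiological measures to one year. The Statistics section is not silent on timing either: it names the model, the outcomes and the time, and that time is one of the four.

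Two things follow if the plan is carried out as written.

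- Three defined endpoint times have no between-arm comparison fixed in advance. Whether to test the earlier scores, and which of them, stays open until the data have been seen.
- The earlier scores have one stated role, as substitutes for missing one-year values. Pain, function and walking distance are expected to change over the first year. An early score is therefore a poor stand-in for a one-year result.

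**Working it through.** **1. The plan's own figures.** Sample size calculation plans for an "expected increase of the success rate from 60% in the closed wedge HTO to 85% in the combined wedge HTO", with α 0.05 and 80% power, and gives 50 per group. The two-sided pooled normal formula without continuity correction gives 49 per group, and 50 per group has power 80.9%. The stated size reproduces. It rests on the dichotomous alignment outcome, so nothing below changes it.

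**2. Endpoint times against modelled times.**

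| Time | Defined as endpoint | In the stated model |
|---|---|---|
| 6 weeks | yes | no |
| 3 months | yes | no |
| 6 months | yes | no |
| 1 year | yes | yes |

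Per scale: 110 × 4 = 440 planned follow-up assessments, of which 110 × 3 = 330 (75%) have no stated comparison. Over three scales, counting KOOS as one score, this is 990 of 1,320.

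**3. How much of this carry-forward uses.** The plan recruits 110 to retain 100, an allowance of 10 patients (10/110 = 9.1%). Each lost patient supplies at most one carried value per scale, so about 10 of the 330 interim values (3%) would enter the one-year analysis. Re-operated patients would add to this; the article gives no expected number.

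**4. What the carried value represents.** The aftercare described at the end of the lateral closing wedge section, for both techniques, is a cast until stitch removal, then a brace and half weight bearing for 6 weeks. A six-week score therefore falls within this restricted period or at its end. Let d be the difference between the carried score and the score that the patient would have had at one year. With m of 55 patients carried forward in an arm, that arm's mean shifts by (m/55) × d.

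- Losses split 5 and 5: each mean shifts by 5/55 = 9% of d. The shifts cancel in the arm difference only if d is the same in both arms.
- All 10 losses in one arm (the extreme): the arm difference shifts by 10/55 = 18% of d.

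The documents give no value for d, so this is a scale for the problem and not an estimate of bias.

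**5. What a repeated-measures model changes.** Take a model with arm, visit, arm-by-visit, baseline and unstructured covariance. If every patient has all four scores and the baseline effect may differ by visit, the predictors are the same at every visit, and the one-year contrast equals that of a separate baseline-adjusted regression at one year. With a single baseline coefficient it is nearly the same. With complete data the one-year result therefore hardly moves. What changes is that the other three times get estimates, and that patients with partial follow-up contribute their observed scores without an assumption of no later change.

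**6. Why one model with one principal time.** Separate tests at every time would be 3 × 4 = 12. If they were independent, the chance of at least one false positive at 0.05 would be 1 − 0.95^12 = 46%, against 1 − 0.95^3 = 14% for three one-year tests. The earlier times should therefore be supportive and not twelve equal claims.

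**The case against.** The case for leaving the plan alone has four parts.

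- **The hypothesis is about one year.** It concerns accuracy of correction and anatomical change, and no recovery-trajectory objective is stated. One principal time also limits multiplicity. Both points stand, and they are why one year should remain the principal contrast. They do not explain why three further times are called endpoints.
- **An article may leave interim summaries to an SAP.** This stands in part. A reader might infer that the early data go unused. The text does not support that: some values are carried forward, and nothing rules out descriptive reporting. The supportable statement is narrower: the article fixes a comparison at one of four endpoint times and no other.
- **A missing visit is not missing data.** A reader might infer that the three-month scores will not be collected. Study procedures says that they will be, the scales can be completed without a clinic visit, and the visit sentence is followed by one on the surgeon's physical examination. What remains is a small gap: the route of collection is not stated.
- **A mixed model is a matter of taste.** Naming one year as the analysed time and the rest as descriptive would also remove the mismatch. That is a fair minimum, but it leaves carry-forward in place.

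A reader might also expect a marked gain in precision from using four scores in place of one. Such a gain belongs to an average over the four times, which is a different quantity from the one-year effect recommended here. It would also need correlations that the documents do not give, and equal correlation between a six-week score under restricted weight bearing and a one-year score is doubtful.

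**Conclusion.** The mismatch is in the text and should be corrected. VAS, KOOS and walking distance are endpoints at four times, the stated model compares the arms at one, and the earlier scores have no stated use except carry-forward. The size is three of four endpoint times without a stated comparison. In addition, about 10 of 110 patients, by the plan's own allowance, could have an earlier score standing as their one-year result. The figure of 10 assumes that losses match the allowance and leaves out re-operated patients.

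The consequence is limited. Only secondary endpoints are touched; the primary alignment outcome and the sample size are unaffected. With complete data the one-year contrast on these scales would be essentially the same under either analysis.

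**What to change.** In Statistics, replace the one-year regression for VAS, KOOS and walking distance with one linear mixed model for repeated measures per scale. Use all four follow-ups, with baseline value, arm, visit and arm-by-visit as fixed effects and an unstructured covariance. Drop carry-forward for these scales. Name one year as the principal contrast and report the arm differences at the other three times, with confidence intervals, as supportive. State whether scores observed after a re-operation enter the model, because carry-forward now covers those patients too.

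In Study procedures, add one sentence on how the three-month questionnaires are obtained, or remove that time from the endpoints.

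The cost is small: a change of wording and slightly more analysis work, in software that the plan already names (SPSS fits this model). The number of patients does not change. The model assumes that missing scores are missing at random given the observed ones. That assumption should be stated, and it is easier to defend here than no change after an early score.

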#### Lateral closing wedge osteotomy (LCW)

For the lateral closing wedge HTO, instrumentation of Allopro (Zimmer; Winterthur, Switzerland) will be used. The common peroneal nerve will be exposed and snared with a nerve band. Next, the anterior part of the proximal fibular head (anterior part of the proximal tibiofibular syndesmosis) will be resected. The osteotomy will be made and the wedge taken out. The osteotomy will be fixated with two staples. At the end of the procedure a fasciotomy of the anterior compartment will be performed to prevent compartment syndrome.

The postoperative treatment for both HTO techniques consists of a pressure bandage for 24 hours and cast immobilization until removal of the stitches, followed by flexion-extension brace protection and 50% weight bearing for 6 weeks. After this period, weight bearing can be built up to 100% based on the pain sensation of the patient, brace use can be reduced to no brace, and physical therapy will be started.

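### The carry-forward rule sets no earliest admissible time, so a six-week KOOS or walking-distance value taken under restricted weight bearing can stand as the one-year result

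*Protocol article*

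**What the plan says.** Secondary study parameters/endpoints lists pain, KOOS and "walking distance (km) at six weeks, three months, six months and one year after surgery". Study procedures repeats the schedule: "walking distance (km) six weeks, three months, six months and one year after surgery will also be obtained".

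The postoperative regimen stands at the end of the section on the lateral closing wedge technique but covers both arms: "The postoperative treatment for both HTO techniques consists of a pressure bandage for 24 hours", then "cast immobilization until removal of the stitches", "followed by flexion-extension brace protection and 50% weight bearing for 6 weeks". Release comes later: "After this period, weight bearing can be built up to 100% based on the pain sensation of the patient". Brace weaning and physical therapy also start only then. The day of stitch removal is not given.

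Statistics requires every randomized patient to be analysed as allocated. For those lost or re-operated, "the last available measurement or the last measurement will be forwarded (Last Value Carried Forward technique". The linear regression for KOOS and walking distance is specified at one year.

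**The concern.** Each rule is reasonable alone; the problem is how they combine. Carry-forward assumes that the last observed value is a fair substitute for the one-year value. For function after an osteotomy, that assumption fails most clearly for a value recorded while the protocol itself limits loading and before physical therapy has begun. Nothing in Statistics stops such a value, or even a preoperative one, from entering the one-year regression.

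At stake is the one-year treatment contrast for KOOS and walking distance. Low carried values dilute a real difference if both arms lose patients equally early. They produce an artificial difference if one arm loses or re-operates more patients early. Carry-forward also treats the substituted values as observed, so the analysis does not reflect the uncertainty they bring.

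**Working it through.** **The plan's own calculation.** The only computed figure is the sample size: 60% against 85%, alpha 0.05, power 80%, 50 per arm. With the pooled-variance formula, two-sided and without continuity correction:

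n = [1.960 × √(2 × 0.725 × 0.275) + 0.842 × √(0.60 × 0.40 + 0.85 × 0.15)]² / 0.25² = 48.9, so 49 per arm.

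This agrees with the stated 50. It rests on the alignment outcome, so the present point does not affect it. The total of 110 against 100 needed allows 10 losses: 10/110 = 9.1%.

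**Timing.** On the plain reading, restriction ends at the day of stitch removal plus 42 days. The six-week measurement is at day 42. The stitch-removal day is an assumption:

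- day 7: ends day 49, week 7.0
- day 10: ends day 52, week 7.4
- day 14: ends day 56, week 8.0
- day 21: ends day 63, week 9.0

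The measurement then falls one to three weeks before release. If the six weeks run from surgery instead, restriction ends on day 42 and the measurement coincides with its end, before loading is built up.

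**Who is exposed.** Only patients whose last value is the six-week one are affected, that is, those lost or re-operated before the next measurement. Study procedures lists clinic visits at six weeks, six months and one year, although scores are also due at three months. If the three-month scores are not obtained separately, the exposed window runs to six months.

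**Size.** Let d1 and d2 be the shares of the arms carrying a six-week value, and R the shortfall of that value from the patient's true one-year value, in SD units. R is assumed; the documents give no figure.

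*Equal loss, d1 = d2 = d.* Each arm mean falls by d × R. With d = 0.091, that is 0.05, 0.09 or 0.18 SD for R = 0.5, 1 or 2. With no true difference the contrast stays unbiased. If there is a true one-year difference but no arm difference at six weeks, the difference is multiplied by (1 − d): 0.5 × (1 − 0.091) = 0.455 SD.

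*Unequal loss, no true difference.* The spurious contrast is (d2 − d1) × R:

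| Loss by arm | R = 0.5 | R = 1 | R = 2 |
|---|---|---|---|
| 5% vs 13% | 0.04 | 0.08 | 0.16 |
| 0% vs 18% | 0.09 | 0.18 | 0.36 |

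With 55 per arm, each row uses about the whole allowance of 10 patients (0.05 × 55 + 0.13 × 55 = 9.9; 0.18 × 55 = 9.9). Both rows therefore assume that every planned loss has six weeks as its last value. The second row is an extreme.

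**The case against.** A reader might infer more: that six-week walking distance and KOOS merely measure the restriction, say nothing about the technique, and should be dropped as endpoints. The document does not support this. The regimen is the same in both arms, so it may compress scores but does not by itself bias a six-week comparison. The techniques differ in fixation and bone handling, and patients under the same restriction could still differ in early function. KOOS here also covers quality of life. Repeated measurement from six weeks to one year describes a recovery course, and the only regression set out for these scores is at one year. Dropping the time point would be a preference.

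A second objection is that few patients are affected. That largely stands: their number is not given, the planned loss is small, and with balanced loss the effect on the contrast is modest. Balance cannot be taken for granted, however. The rule also covers re-operation, and Other study parameters counts hardware removal as such. The combined technique uses three staples and the closing wedge two, and the Discussion says opposite-cortex fracture is frequent with the closing wedge. No rates or timing are given, so this shows only that unequal re-operation is plausible.

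A third objection is that unrestricted carry-forward is a general missing-data weakness. That is true, but the rule is stated in the document rather than left open, and here the document's own regimen gives a reason to expect the carried value to be low.

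**Conclusion.** The point holds against the carry-forward rule, not against the measurement schedule. As written, Statistics lets a six-week functional value stand for one year, and on the plain reading of the regimen that value was taken under prescribed restriction. Counting the six weeks from surgery softens this but does not remove it.

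The effect is small if early loss is balanced and within the planned allowance. It can matter if early loss or re-operation differs by arm: 0.08 to 0.16 SD in the 5% against 13% case with R of 1 to 2. These sizes rest on the assumed shortfall R and on all planned losses carrying six-week values, so they are upper illustrations rather than estimates. Only KOOS and walking distance at one year are concerned; the alignment sample size is unaffected.

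**What to change.** In Statistics, state that six-week and preoperative KOOS and walking-distance values are not carried forward to one year. Barring them without a substitute would leave some randomized patients with no outcome, so name the replacement. One option is a mixed model for repeated measures using all collected time points, with the one-year contrast as its target. The other is multiple imputation using baseline and the earlier scores. To keep every randomized patient in, the mixed model should take the baseline score as one of the repeated measurements; otherwise patients with no postoperative value drop out. State whether values observed after re-operation are used or treated as missing. Keep last value carried forward as a sensitivity analysis only.

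In Secondary study parameters/endpoints and Study procedures, keep the six-week measurements and describe them as recovery-course data. Reconcile these sections with the postoperative paragraph on the day from which the six weeks run. No change to postoperative care is proposed.

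The cost is a few sentences of wording, somewhat more analysis work, and reliance on a missing-at-random assumption. No additional data need to be collected.

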### Other study parameters

Potential confounding parameters, such as opposite cortex fractures, demographic data, length, weight and BMI will be recorded. Adverse events like re-operations, including hardware removal, will also be recorded**.**

### Randomization, blinding and treatment allocation

For randomization a restricted randomization/blocked randomization (2×10 patients in one block) method will be used. The same number of patients will be allocated to each surgical treatment group. Two random allocation sets (for the CWO and the LCW) will be generated by a computer. These allocations are then sealed in consecutively numbered opaque envelopes. Once the patient has given consent to be included in the trial, the HTO technique (CWO or LCW) is randomly assigned by opening the next sealed envelope.

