### Study population

Patients visiting the outpatient clinic of the Orthopedic Department who have an indication to undergo HTO because of osteoarthritis of the medial compartment of the knee with varus alignment will be included if they meet the following criteria: radiologically confirmed medial compartment osteoarthritis, medial joint pain, 6-12° varus alignment and age 18 and older. Exclusion criteria are: symptomatic osteoarthritis of the lateral compartment, rheumatoid arthritis, range of motion of the knee joint under 100°, flexion contracture more than 10°, grade 3 collateral laxity (Insall), history of fracture or previous open operation of the lower extremity, mental incapacity, or inability to fill in the questionnaires in Dutch.

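### Blocks of 20 do not divide 110 patients, so equal groups are not guaranteed, and the single disclosed block size leaves a modest, conditional selection risk

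*Protocol article*

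**What the plan says.** The section on randomization, blinding and treatment allocation describes one scheme: a "restricted randomization/blocked randomization (2×10 patients in one block) method will be used". It adds that "The same number of patients will be allocated to each surgical treatment group". The computer-generated allocations go into opaque, sealed, consecutively numbered envelopes, and the next one is opened after consent.

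The sample size section asks for 50 patients per group and, to allow for loss to follow-up, says that "a total of 110 patients will be included in the study".

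Three other sections supply context. The study runs in one orthopedic department (Study design). Two surgeons, each using both techniques, perform all operations (Interventions). Candidates are clinic patients "who have an indication to undergo HTO because of osteoarthritis of the medial compartment of the knee with varus alignment" (Study population), and an orthopedic surgeon does the physical examination at the visits, including the preoperative one (Study procedures). The article does not say who recruits, who rules on eligibility, who opens the envelopes, or whether those people know the block size.

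**The concern.** There are two issues of unequal weight.

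- **Consistency.** A block of 20, a total of 110 and equal group sizes cannot all be guaranteed together. Balance is assured only at the end of a complete block, and 110 is not such a point.
- **Concealment.** When one block size is used throughout and is known, anyone who counts past assignments can sometimes deduce the next one, however opaque the envelope. Here the two operators between them know every past assignment. If that knowledge reaches the people who decide whom to approach, a borderline patient could be offered entry or deferred according to the technique expected next, and the groups could then differ at baseline. Opening the envelope after consent does not prevent selection before consent is sought.

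**Working it through.** **Inputs.** Block of 2 × 10 = 20, ten per arm (randomization section); total 110, 50 needed per group, success 60% versus 85%, α = 0.05, power 80% (sample size section). Sidedness is not stated and is taken as two-sided.

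**1. The plan's own figure.** With the pooled-variance formula for two proportions and no continuity correction:

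n = [1.960 × √(2 × 0.725 × 0.275) + 0.842 × √(0.60 × 0.40 + 0.85 × 0.15)]² / 0.25² = (1.238 + 0.510)² / 0.0625 ≈ 48.9, so 49 per group.

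The stated 50 is reproduced. Going from 100 to 110 implies a loss of 10/110 = 9.1%.

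**2. Does the block size fit the total?** 110 / 20 = 5.5. Five blocks fill exactly (50:50), and ten patients fall in an incomplete sixth.

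**3. Split in the half block.** The number k assigned to one arm among the first 10 of a balanced block of 20 is hypergeometric, P(k) = C(10,k)² / C(20,10), with C(20,10) = 184,756.

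| Final split | Calculation | Probability |
|---|---|---|
| 55:55 | 252² / 184,756 = 63,504 / 184,756 | 34.4% |
| 54:56 either way | 2 × 210² / 184,756 = 88,200 / 184,756 | 47.7% |
| Gap of 4 or more | remainder | 17.9% |

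The gap is 0 or 2 with probability 34.4% + 47.7% = 82.1%. The expected gap is 1.7 patients, and the worst case is 60:50.

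**4. Effect on power.** If all 110 are analyzed, power is 84.5% at 55:55 and lies between 84.0% and 84.6% over every split from 50:60 to 60:50.

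**5. Allocations certain in advance.** In a complete block of 2m, the expected number forced because one arm is used up is 2m/(m + 1). For m = 10 this is 20/11 = 1.82, so five blocks give 9.1. The half block adds none, since an arm cannot run out before its tenth patient. In total, 9.1/110 = 8.3%. This needs someone who knows the block size and every past assignment.

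**6. Best guess of the next allocation.** The strategy is to guess the arm that is behind. Expected correct guesses in a complete block are m + (4^m / C(2m,m) − 1)/2. For m = 10 this is 12.34 of 20 (61.7%). The half block yields 5.47 of 10. Over the trial: (5 × 12.34 + 5.47)/110 = 67.2/110 = 61%, against 50% by chance. This needs only running totals per arm.

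**7. Other block sizes.**

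| Scheme | Correct guesses |
|---|---|
| Fixed 4 | 71% (33% of allocations forced if the size is known) |
| Fixed 10 | 65% (16.7% forced if the size is known) |
| Varying 4, 6, 8 | about 68% |
| Varying 8 to 14 | about 65% |
| Varying 16 to 24 | about 62% |

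Varying the size removes certainty at block ends when boundaries are unknown, but it does not lower the guess rate. Only keeping blocks large does that.

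**The case against.** **Equality.** The sentence on equal numbers can be read as simply describing a 1:1 design, and a typical gap of two patients has no consequence for power. That stands: this part is a matter of internal consistency. If 2 × 10 meant two blocks of 10, then 110/10 = 11 complete blocks and equality would hold. The wording puts 2 × 10 in one block, however, and blocks of 10 would roughly double the forced share (16.7% against 8.3%).

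**Predictability.** A block of 20 is large, and computer generation, opaque numbered envelopes and opening after consent are sound practice. About 92% of allocations are never certain, and a 61% guess rate requires someone to track both surgeons' cases. This also stands, and it is why the risk is called modest.

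**Who recruits.** A reader might infer that the operating surgeons enroll patients and can foresee assignments while judging eligibility. The article does not support this. It says who operates, and that an orthopedic surgeon examines patients, which makes a role in recruitment plausible but does not establish it. Such operational detail is commonly left to the full protocol, so its absence is not a fault here.

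What survives is that the article does fix and disclose a single block size, and that size does not fit the stated total.

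**Conclusion.** The point holds in a limited form. Blocks of 20 with 110 patients do not guarantee the stated equality; exact balance occurs about one time in three. It would be too strong to say that equal allocation fails outright, because the gap is at most two patients with probability 82% and power changes by less than one percentage point.

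The fixed, disclosed block size leaves a modest selection risk: about 9 of 110 allocations certain and about 61% guessable. This rests on three assumptions: that 2 × 10 means one block of 20, that all 110 are enrolled in a single unstratified sequence, and that those who recruit learn past allocations and, for the certain ones, know the block size. The third is not established by the article. No bias in the primary outcome has been quantified. The change is worth making because it is cheap and the two operators necessarily know each assignment they carry out.

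**What to change.** Replace the single block size with computer-generated permuted blocks of randomly varying but large size, for example even sizes from 16 to 24, that sum to exactly 110 with 55 per arm (24 + 22 + 24 + 20 + 20 = 110 is one such set). Withhold the sizes and block boundaries from those who recruit and operate. If recruitment has begun, apply this to the unused envelopes only, so that the final totals reach 55:55. Do not use small blocks.

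**Cost:** regenerating the list and envelopes; no extra patients or visits.

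**Gain:** block-end allocations are no longer certain, and the stated equality holds if all 110 are enrolled.

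**Limits:** the guess rate stays near 62%. Anyone who knows that the total is 55:55 could still deduce the very last assignments, on average 2m/(m + 1), or about 1.8 for a final block of 16 to 24, compared with about 9 now.
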